## Materials & methods

### Ethical considerations

The study adhered to the SPIRIT reporting guidelines (S1 Checklist). Approval for the study was granted by the Sri Jagannath Healthcare and Research Center–Independent Ethics Committee (approval number: SJHRC–N4/22/OCT/07), and it was registered with the Clinical Trials Registry of India (registration number: CTRI/2022/12/048416). The protocol described herein is version 1 dated December 23, 2022. Changes to the protocol arising from peer review will be updated as version 2 and appropriate updates will be made to the protocol on the Clinical Trials Registry of India; the ethics committee will also be apprised of the changes and provided a copy of the revised protocol. Participants will provide written informed consent, and their next of kin will provide oral informed consent before commencement of their participation.

### Participants

Persons meeting the criteria for the definition of a houseless person—someone who does not live in a building or "census houses," but rather in the open or seeks shelter in public places such as railway stations, under flyovers, places of worship, etc.—according to the 2011 Census of India, and residing in Chennai or Dhanbad, India during and after the Unlock 2.0 phase of the COVID-19 pandemic in India, aged >18 years will be recruited. Persons with a formal diagnosis of anxiety, depression, and any other mental illness will be excluded from the study and provided access to evidence-based treatments. All PEH availing the services of Samanjasa Foundation in Chennai and Dhanbad will be approached to participate in the study; the study information will be disseminated through the case workers. During earlier studies we found that this strategy ensures nearly 90% response rate; therefore, we are expecting a similar enrolment rate in this study as well. The participants will be divided into four groups—the Bhagavad Gita (Gita), Kuchipudi dance (Kuchipudi), both Bhagavad Gita and Kuchipudi dance (Both), and control groups—in a 1:1:1:1 ratio. The participant identification number, group assignment, four copies of a questionnaire with pre-filled participant ID and follow-up date, meeting schedule, and Zoom meeting link will be sealed in a small envelope and the envelopes will be placed in a fishbowl and shuffled. The participant ID will be generated in a random order by an independent statistician using a pseudo-random number generator script in Python 3.9.13. Group assignment will be generated in sequence by the independent statistician; the participant ID generated first will be associated with the Gita group, the second with the Kuchipudi group, the third with the Both group, the fourth with the Control group, the fifth with the Gita group, and so on. The project staff will fill and seal the envelopes with the respective contents. Once a participant provides written informed consent to participate in the study, they will be asked to pull an envelope from the fishbowl and not reveal its contents to the research team. They will also be instructed not to read the questionnaires until the sessions scheduled for the purpose of filling them out. To monitor and minimize the risk of contamination, especially given the potential for participants within the same community to communicate, the project staff will send weekly text messages to the participants regarding not sharing details about the intervention with anyone, including their family members. Additionally, the project staff will randomly contact three participants from each group via a phone call every two months and ask them if they had heard anything about the interventions in the other study groups. Furthermore, during community events and interactions, case workers will be asked to assess the level of knowledge regarding the intervention among the PEH. The participant journey is illustrated in Fig 1.

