The Bhagavad Gita offers practical guidance on navigating daily stressors [12]. Within the realm of RSIs, recent studies offer insights into the potential relevance of the Bhagavad Gita’s teachings for psychological well-being among adolescents [13] and individuals coping with chronic illnesses [14]; however, these studies do not encompass a synthesis of empirical data to validate their findings. Recently, Das and Behura proposed that learning the Bhagavad Gita could improve the stress coping abilities of healthcare providers during the COVID-19 pandemic, drawing parallels between their experiences and those of war veterans; however, this study also lacked empirical substantiation [15].

Considering that homelessness also poses significant challenges to human health, including mental health, and our organization’s volunteers had noted that a significant number of PEH had turned to spirituality as a coping mechanism to deal with the mental health challenges brought about by the COVID-19 pandemic, we hypothesized that imparting the teachings of the Bhagavad Gita as a one-time intervention could enhance the psychological resilience of PEH.

This study aims to bridge the knowledge gap concerning the effectiveness of Hindu RSIs in a previously unexplored population—PEH—by evaluating the impact of learning the Bhagavad Gita on reducing psychological distress among PEH. Engaging in Kuchipudi dance practice as a hobby will function as a positive control, while abstaining from stress-reducing activities will serve as the negative control. In other words, the central research question is, what is the impact of learning the Bhagavad Gita on reducing psychological distress among PEH, and how does this compare with the impact of engaging in Kuchipudi dance practice as a hobby? This multi-site parallel-group RCT seeks to comprehensively assess both short and long-term outcomes. Table 1 outlines the research inquiries guiding our study and presents potential interpretations of the anticipated results.

**Table 1 pone.0310795.t001:** Study design.

Question	Hypothesis	Sampling plan	Analysis plan	Interpretation given to different outcomes

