### Plan for handling missing data and protocol deviations

In case we are unable to recruit the required number of participants for the study from only Chennai and Dhanbad during the envisaged recruitment period, we will open the recruitment to the remaining locations that Samanjasa Foundation operates in, i.e., Hyderabad and Bhubaneshwar, India, and extend the recruitment period by another 4 weeks. Consequently, the timelines for the baseline measurements, interventions, and all post-intervention measurements will be delayed by 4 weeks. To minimize missing data, the participants will be given clear written instructions in their mother tongue and the project staff will regularly follow-up with the participants to ensure that they will not drop out of the study. Before the scheduled meetings, the participants will receive text messages and a phone call reminder from the project staff. Depending on post-hoc power analysis results, missing data will be handled either by complete case analysis or multiple imputation. Protocol deviations may result from technology failure and failure of the participants to comply with the interventions. The clear written instructions to the participants in their mother tongue and regular follow-up by project staff will help facilitate participant compliance. In case of technology failure, the project staff will video call the participants through WhatsApp, as the participants are more familiar with it than with Zoom. To prevent technology failure due to running out of data, all participants will receive an unlimited data recharge with one month validity one day before the scheduled baseline, delayed post-intervention, and long-term follow-up measurements. This can also serve as an incentive to the participants to attend the scheduled measurement sessions and help minimize missing data. In case of technology failure due to other reasons, the participants will be offered catch-up sessions before the next scheduled session.

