### Risk mitigation strategy

As PEH are a vulnerable group, several risk mitigation strategies have been put in place to ensure the safety and wellbeing of the participants. These are as follows:

Informed Consent will be obtained from each participant, after providing them with oral and written information clearly explaining the purpose, procedures, potential risks, and benefits of the intervention. To ensure that the participants understand their rights, the voluntary nature of participation, and their ability to withdraw at any time without consequences, they will be asked to repeat the information in their own words, orally and in writing, to the research team.To facilitate compliance with the intervention, the project staff will be drawn from the volunteers who are involved in the day-to-day activities of our organization, engaging regularly with our PEH clients. The trained teachers who will administer the interventions will be from external organizations; this will help the participants engage with organizations other than our own, thus deepening their engagement with civil society. To maintain objectivity and minimise the possibility that the participants may feel coerced to participate in the research on account of being approached by volunteers they frequently engage with, the research team is kept separate from the client engagement teams in our organization.Secure online platforms will be used in adherence to data protection regulations of our organization to safeguard personal data of all stakeholders. The smartphones used for sending and receiving correspondence and photographs of the filled K10 questionnaires will be those provided by the organization. The project staff will not use their personal phone numbers for communication with the participants under any circumstance.Keeping the culture of India in mind, the participants will be asked to provide oral consent from their next of kin. This will be recorded on the consent forms and countersigned by the participant. In case the participant is unable to read or sign their name, the consent process will be conducted in the presence of two healthcare professionals who are not related to our organization. A blank informed consent form in English and Hindi has been provided as S1 File. The informed consent forms in other languages (Tamil, Telugu, and Bengali) are true translations of the informed consent form in English.The participants’ technological access and proficiency will be assessed at the time of obtaining consent to ensure that they can fully engage with the online intervention. In case technological proficiency needs to be improved, digital literacy training and training on the digital platforms to be used in the intervention will be provided.

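### A multi-city trial allocates from a single unstratified fishbowl, so arm balance within each city is left to chance, and the analysis names no city term

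*Protocol article*

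**What the plan says.** The Introduction gives the design: "This multi-site parallel-group RCT seeks to comprehensively assess both short and long-term outcomes". Under Participants, eligible people are those "residing in Chennai or Dhanbad, India", to be divided "in a 1:1:1:1 ratio" among the Gita, Kuchipudi, Both and Control arms. The independent statistician puts the IDs in random order and assigns arms to them in fixed rotation: "the participant ID generated first will be associated with the Gita group, the second with the Kuchipudi group", and so on. Project staff fill the envelopes, which "will be sealed in a small envelope and the envelopes will be placed in a fishbowl and shuffled". A participant draws after giving written consent. The section speaks of one fishbowl throughout and mentions no stratum, block or separate set for a city.

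The plan for missing data and protocol deviations adds a fallback if recruitment is short: "we will open the recruitment to the remaining locations that Samanjasa Foundation operates in, i.e., Hyderabad and Bhubaneshwar, India". It does not say how envelopes would reach a city that opens late.

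On analysis, the Data analysis and Primary analysis sections specify a GEE with robust standard errors, and the latter adds an exchangeable correlation. Table 1 names continued practice and religion as covariates. City appears in none of these places.

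**The concern.** Rotating arms over the ID list gives equal totals, but shuffling the envelopes removes whatever balance the rotation would have given over shorter runs. What remains is a random draw without replacement from one pool, with equality enforced only over the full set. Any part of that pool, such as one city's participants, those enrolled before recruitment stops, or those in a late-opened city, is a random subset with unequal arm counts.

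City may carry differences in local conditions and staff that shift K10 scores. If it does, chance differences between arms in their city mix add noise to every comparison between arms. Design and a model term can remove most of that noise, and the article describes neither.

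**Working it through.** **Inputs from the protocol article.** Recruitment target 256, or 64 per arm (Sample size calculation). Four arms in equal ratio, one shuffled pool and two cities (Participants). Planned difference 7 K10 points (Sample size calculation). The target is taken as stated, 4 × 64 = 256; nothing here depends on how 64 was derived.

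**Assumption.** The number of participants per city is not given, so a range is shown.

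**Arm counts within a city.** If c of the 256 envelopes are drawn in one city, the count for one arm is hypergeometric, with mean c/4 and variance c × 0.25 × 0.75 × (256 − c)/255.

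- c = 128: mean 32; variance 24 × 128/255 = 12.05; SD 3.47.
- c = 80: mean 20; variance 15 × 176/255 = 10.35; SD 3.22; 95% range 14 to 26.

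Simulation of the draw (20,000 repeats per city size) gives the spread across all four arms:

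| Participants in the city (assumed) | Expected per arm | 95% range, one arm | Largest minus smallest arm: median | 95th percentile |
|---|---|---|---|---|
| 128 | 32 | 25–39 | 8 | 15 |
| 86 | 21.5 | 15–28 | 7 | 14 |
| 64 | 16 | 10–22 | 7 | 13 |
| 51 | 12.75 | 8–18 | 6 | 12 |

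With 128 in the city, the gap is 10 or more in about 34% of draws. At every size in the table, a gap of 1 or less occurs in under 2% of draws.

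**Overall ratio if recruitment stops short.** If 216 of the 256 envelopes are drawn, the variance for one arm is 216 × 0.1875 × 40/255 = 6.35, SD 2.5 around 54. The largest-minus-smallest gap has median 6 and 95th percentile 10.

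**What this does to a comparison.** With c = 128, the covariance of two arms' counts is −128 × 0.0625 × 128/255 = −4.02. The variance of their difference is 2 × 12.05 + 2 × 4.02 = 32.1, SD 5.67. Divided by 64, this is an SD of 8.9 percentage points in city share between two named arms. If the cities differed by 5 K10 points (an assumption), the resulting chance shift has SD 5 × 0.089 = 0.44 points, and its absolute size has a 95th percentile of about 0.86. The planned difference is 7 points.

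**With balanced sets per city.** The gap in any city cannot exceed what one unfinished set allows: 1 for sets of four, 2 for sets of eight.

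**The case against.** Unstratified randomisation is valid. Expected arm shares are equal in every city, including one that opens late, because what remains of a shuffled pool is itself a random subset. Ordinary standard errors already allow for chance imbalance, and a stable difference in K10 level between cities would largely cancel in change from baseline. The shift calculated above is small beside 7 points. An article may also leave the full covariate list to a fuller plan. All of this stands, and it limits the point to precision and chance imbalance. It does not remove the point, because the allocation is described step by step and has no city element.

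Three stronger readings are tempting, and the documents do not support them.

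- **Arms will be badly unbalanced by city.** A split such as 25 of 64 (39%) against 39 of 64 (61%) needs a gap of 14. With 128 in the city, a named pair of arms reaches that in about 1.7% of draws, and some pair among the four in about 8%. It is a tail case.
- **The sealed materials cannot match the drawer's language.** Consent forms exist in English and Hindi, and "The informed consent forms in other languages (Tamil, Telugu, and Bengali) are true translations". But no section gives the language of the sealed questionnaires, the schedule or the sessions. The mother-tongue commitment concerns written instructions, and staff guide participants through the form. Multilingual forms or sessions would be consistent with the text.
- **Staff would swap materials after a draw, or language imbalance would fall mainly on the Gita arm.** Neither is in the text.

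**Conclusion.** The point holds as a worthwhile design improvement, not as a flaw that invalidates the comparison. As described, one pool serves two to four cities, balance within city is not guaranteed, and the 1:1:1:1 ratio is exact only when every envelope is used. Under an assumed even split between two cities, an arm's count in one city ranges from 25 to 39 around 32, and the typical gap between the largest and smallest arm is 8. The effect on a contrast depends on how far K10 differs between cities, which the documents do not give; at an assumed 5 points it is an SD of 0.44 K10 points. The conclusion rests on reading the single fishbowl literally. If each city in fact receives its own balanced envelope set, only the statement of that procedure and the city term are needed.

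**What to change.** Before enrolment, have the independent statistician generate a separate list for each city, with equal numbers per arm in small balanced sets, and fill one envelope set per city. A city that opens late should receive new balanced sets of its own, not leftovers. State this under Participants, and add city as a factor in the GEE in the Data analysis and Primary analysis sections.

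The cost is preparing and labelling envelopes per city, plus one model term (three if all four cities open). Very small sets can become partly predictable if earlier allocations leak, so set sizes should vary and be withheld from those who enrol participants.

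The authors should also confirm in which languages the sealed questionnaires, the schedule and the linked sessions will be provided. Sets prepared per city would make local-language versions easy to supply if they are needed.

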### Interventions

The participants in the Gita group will be imparted the teachings of the second chapter of the Bhagavad Gita (all verses) for 1 week, for 60 minutes per day. The teachings of the Bhagavad Gita will be imparted by a trained teacher and the second chapter has been chosen as it is said to contain the essence of the entire Bhagavad Gita [16]. The participants in the Kuchipudi group will be taught the Kuchipudi dance choreography to a popular devotional song (“Sivashtakam”, choreographed by Padma Bhushan [name] [name], song duration is approximately 10 min) for 60 minutes per day by a trained teacher for 1 week. Every day for 1 week, the participants in the Both group will be taught the Kuchipudi dance choreography to a popular devotional song (“Vandanamu Raghunandana”, choreographed by Kala Tilakam [name], song duration is approximately 5 min), which is shorter in duration than the song used in the Kuchipudi group, for 30 minutes by a trained teacher, followed by imparting the teachings from selected verses of the second chapter of the Bhagavad Gita (Verse 40–72) for 30 minutes by a trained teacher. The participants in the control group will receive no intervention. The participants will be instructed to join their assigned groups at the scheduled meeting times using the meeting link in their sealed envelopes. Apart from the teaching sessions, meetings will also be scheduled one day before the start of the teaching sessions, one day after the end of the teaching sessions, 40 days after the end of the teaching sessions, and 1 year after the end of the teaching sessions for the purpose of recording the baseline, immediate post-intervention, delayed post-intervention, and long-term follow-up measurements, respectively. For participants in the control group, the meeting schedule will consist of only the four measurement sessions.

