### Data collection and management procedures

During each scheduled measurement session, the participants will be asked to take the questionnaire they were provided with in the sealed envelopes given to them at the time of enrolment that is pre-filled with the date of the appropriate measurement session. They will then be asked to hold the questionnaire sheet with the date visible to the camera and trained research support staff will check that each participant is holding the correct questionnaire. They will then walk the participants through how to fill in the questionnaire. Once they confirm that the questionnaires have been filled, they will walk the participants through how to take a photograph of the sheet and send the photo to the staff member via WhatsApp. Once the staff member receives legible photographs of the filled questionnaires from all participants, the meetings will be ended. The project staff will then save the photographs into as portable document format files on a secure computer situated in the research office of our organization and print out the same for our records. Our organization’s policy is to store both soft and hard copies of all research material—the soft copies are stored for a period of 2 years and the hard copies are stored for a period of 10 years. The research team will have unrestricted access to the final dataset.

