### Timeline

Engagement with PEHs begins in Week 1, followed by a 4-week recruitment period. Baseline measurements will be conducted in Week 5, interventions in Weeks 6–7, and post-intervention assessments in Weeks 8, 12, and 56. Interim analysis shall be conducted in Weeks 13–19, and results will be published as the Stage II of this registered report. Final analysis will be conducted in Weeks 57–61, and results shall be published as a brief report. Conferences, meetings, workshops, and other community engagement events to disseminate the results of the study will be ongoing indefinitely, starting from the date of publication of the interim analysis as a registered report. The detailed timeline is shown in Fig 3.

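### Participants can know their arm, for up to several weeks, before the self-reported baseline K10 is taken, because the assignment travels in the same envelope as the baseline form

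*Protocol article*

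**What the plan says.** The Participants section of the protocol article lists what is sealed together: "The participant identification number, group assignment, four copies of a questionnaire with pre-filled participant ID and follow-up date, meeting schedule, and Zoom meeting link". The envelope is drawn at consent: "Once a participant provides written informed consent to participate in the study, they will be asked to pull an envelope from the fishbowl". Participants are asked to keep the contents from the research team, and one further restriction follows: "They will also be instructed not to read the questionnaires until the sessions scheduled for the purpose of filling them out". It covers the questionnaires, not the assignment.

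The Interventions section makes the envelope necessary for attendance: "The participants will be instructed to join their assigned groups at the scheduled meeting times using the meeting link in their sealed envelopes". It also says that a control participant's schedule lists only the four measurement sessions. On the timing of baseline it says that "meetings will also be scheduled one day before the start of the teaching sessions". The Data collection and management procedures section takes the form for every measurement session from the same envelope: "the participants will be asked to take the questionnaire they were provided with in the sealed envelopes given to them at the time of enrolment".

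The Timeline section gives a 4-week recruitment period after engagement begins in Week 1, and then: "Baseline measurements will be conducted in Week 5". The section on missing data and protocol deviations allows recruitment to be extended by 4 weeks, with baseline delayed to match. The Blinding section covers teachers, project staff and the research team; it does not list participants.

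**The concern.** Once teaching starts, participants in this trial cannot be blinded to their arm. At baseline they could be, and the planned order of steps gives that up. K10 is a self-report scale, and the strengths and limitations section itself acknowledges response bias. A participant who has learned that they will get classes, or that they will get none, may answer the first K10 differently for that reason alone.

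Baseline is the reference for much of the analysis. The Primary analysis section compares each intervention group with control and compares time points, including pre-intervention, within each intervention group. Hypotheses 2 and 4 in Table 1 compare decreases from baseline between arms. A baseline that allocation has already touched is no longer a clean starting point for these contrasts, and analysis cannot fully repair it afterwards.

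There is a second, smaller exposure. Anyone who withdraws on learning their arm does so before a K10 value exists, so multiple imputation would have no K10 measurement from that person to work with.

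**Working it through.** **Order of steps.** (1) Written consent. (2) The envelope is drawn; it contains the assignment, schedule, link and all four K10 forms. (3) The link and the baseline form are taken from the envelope. (4) Baseline K10 is completed. The article never says when the envelope is opened, so opening before baseline is an inference. It is a firm one, because step 4 cannot happen without step 3. Even a participant who waits until the session has the assignment in hand before answering. For controls the schedule alone discloses the arm.

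**Length of the gap.** With a 4-week recruitment period ending about when baseline is taken in Week 5, the gap runs from a few days for the last person enrolled to about 3–5 weeks for the first, depending on how the weeks are counted. With the 4-week extension the upper end becomes about 7–9 weeks.

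**Illustration of size.** The plan gives no figure for this bias, so there is none to reproduce.
- From the Sample size calculation section: n = 54 per group, ρ = 0.5.
- Assumed: K10 SD of 8, 10 or 13 (the article gives none); a baseline shift b of 1 or 2 points between two arms; no true effect; none of the shift left at follow-up; an unadjusted two-sided 0.05 test of the difference in change.

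SE = SD × √(2(1 − ρ)) × √(2/n). With ρ = 0.5 the first root is 1, so SE = SD × √(2/54) = 0.1925 × SD.

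False-positive rate = P(Z > 1.96 − b/SE) + P(Z < −1.96 − b/SE).

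| SD | SE | b = 1 | b = 2 |
|---|---|---|---|
| 8 | 1.54 | 0.100 | 0.255 |
| 10 | 1.92 | 0.081 | 0.180 |
| 13 | 2.50 | 0.068 | 0.126 |

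**Persistence.** If a fraction p of the shift is still present at follow-up, it cancels in the change score and only (1 − p)b remains. At SD 8 with p = 0.5, b = 1 acts as 0.5 (0.5/1.54 = 0.325; rate 0.062) and b = 2 acts as 1 (rate 0.100).

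**Direction.** At SD 8 and b = 1 the two tails are 0.095 and 0.005; at b = 2 they are 0.254 and 0.001. Nearly all the excess lies on one side. If controls report more distress at baseline because they are disappointed, or active participants less because they are hopeful, the control group's later decrease looks larger, and the excess rejections favour control. An opposite shift would put them on the side of the interventions.

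**The case against.** The strongest reply accepts the order of steps and disputes the consequences. Much of it stands.

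- **A reader might infer that the plan inflates false claims of benefit.** The documents do not support that. The most natural mechanisms work against the interventions, and nothing in the article establishes a direction.
- **A reader might take 10% and 25% as the error rates of this trial.** They come from the lowest SD in the assumed range, an undocumented shift and complete loss of that shift by follow-up. Participants know their arm at follow-up too, so part of any reporting shift may persist and cancel. The planned Bonferroni correction for pairwise comparisons is also left out of the illustration.
- **A reader might say that all four hypotheses are compromised as comparisons between arms.** Hypothesis 1 is within-group. Hypothesis 3 compares those who continue practice with those who do not, inside each group, so a shift common to an arm cancels. Hypotheses 2 and 4 compare active arms with each other, where seeing a schedule without classes plays no part. The argument has most force for the comparisons with control.
- **A reader might object that baseline is spoiled as an adjustment covariate.** The covariates that Table 1 names are continued practice and religion; baseline K10 is not among them.
- **Loss before baseline that differs by arm is a possibility, not a forecast.** All participants get reminders and a data recharge before baseline, which lowers the risk without removing it.

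What the reply does not answer is that this exposure is avoidable. The contamination checks concern knowledge of other arms' interventions, and no other section withholds a participant's own assignment until baseline.

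**Conclusion.** The point holds as an avoidable weakness in the order of procedures. On the documents' own text, participants can know their arm before the self-reported baseline K10, by days to about 3–5 weeks, or about 7–9 weeks if recruitment is extended. Any allocation-related shift that fades by follow-up enters the intervention-versus-control contrasts and the within-group changes and, to a lesser degree, the active-versus-active contrasts of hypotheses 2 and 4.

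The documents fix neither the direction nor the size of that shift. The illustrative false-positive rates, about 7–10% for 1 point and 13–25% for 2 points, rest on the assumed SD range of 8 to 13 and on no persistence. They show that a small shift could matter, not that one will occur. The case for acting is that the exposure serves no purpose and costs very little to remove.

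**What to change.** Adopt one of two changes.

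1. **Complete the baseline K10 at the consent visit, before the envelope is drawn.** Knowledge of allocation then cannot affect it. The cost is that baseline sits up to about five weeks before the classes, or longer if recruitment is extended.
2. **Keep baseline where it is and seal the assignment, class schedule and class link in an inner envelope, opened only after staff have received the baseline form.** The outer envelope carries the questionnaires and a baseline-session link that does not reveal the arm. The cost is a second envelope and class details that arrive one day ahead. If arms share a baseline session, it must be run so that they do not discuss the interventions, because the protocol otherwise works to limit contact of that kind.

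Under either option, state that everyone who drew an envelope counts as randomised, so that withdrawals before baseline are reported by arm. The sample size does not change. The Ethical considerations section already provides for a version 2 of the protocol, and the change can go there.
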